#### Feasibility and acceptability Questionnaire (FAQ)

At the end of the self-management intervention participants will be asked to complete a semi-structured qualitative feasibility and acceptability questionnaire (see Additional File 3). This questionnaire, specifically developed for this study by the research team, consists of 5 questions made up of fixed choice responses and free text to provide participants with an opportunity to expand on their responses. The questions relate to the feasibility of the intervention for adolescents, the perceived benefits of participating in the program and their level of satisfaction. If shown to be successful in this RCT, the information obtained from this questionnaire, together with the findings from our systematic review, will be used to improve the self-management program delivery and implemented in the future design and development of the revised adolescent-friendly version of the self-management program.

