### Objectives and hypothesis {7}

#### Primary research question

Does a modified adult chronic condition self-management program plus standard care improve therapy adherence in adolescents aged 15–18 years with a chronic condition compared to standard care only?

The *primary objective of this stud*y is to investigate the effectiveness via adherence of a modified adult chronic condition self-management support program in an adolescent population with a chronic condition within a tertiary pediatric hospital setting, compared to those receiving routine care services in the same setting using standardized markers of improvement in control of their chronic illness.

The *secondary objectives* include the use of routinely collected data on the number of unplanned or unscheduled health care or emergency department visits, together with questionnaire measures of quality of life, self-efficacy, time management, health-related distress, and feasibility and acceptability of the program to further refine its delivery under clinical conditions.

*Study hypothesis* to be tested is that a modified adult-focused, generic chronic condition self-management support program provided to adolescents with a chronic condition who are in the active phase of transition to adult services would:Be more effective than standard usual care in achieving adherence to chronic condition management as measured by quantitative condition-specific validated markers of improvement in illness control as described in Table 1.Be more effective than standard care in improving more global quality of life, self-efficacy, time management, and in reducing health-related distress as described in Table 2.

**Table 1 Tab1:** Markers of illness control

Chronic condition	Measures of illness control	Definition of improvement^*^
Cystic fibrosis	▪ FEV1	FEV1% of predicted increased by ≥ 10%
Type 1 diabetes mellitus	▪ HbA1c	Absolute decrease in HbA1C by ≥ 1% (e.g., 9% reducing to 8%)
Inflammatory bowel disease	▪ Weight	Absolute increase in weight by ≥ 5%
Chronic kidney disease	▪ GFR	Absolute increase in GFR by ≥ 5%
Asthma	▪ FEV1	FEV1 % of predicted increased by ≥ 10%
Epilepsy	▪ Number of seizures	Based on individual and type of seizure as negotiated with treating Neurologist.

Abbreviations measures of illness control: *FEV1 (%)* forced expiratory volume in 1 s, *HbA1c* glycosylated hemoglobin (mmol/mol), *GFR* glomerular filtration rate (mL/min)

Weight (kilograms)

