^*^Sustained improvement in measure of disease control over a 12-month period from baseline

**Table 2 Tab2:** Schedule of enrolments, interventions, and assessments

Procedure												
**Measure**	**Baseline**		**3 months**		**6 months**		**9 months**		**12 months**		**18 months**	
	**I**	**C**	**I**	**C**	**I**	**C**	**I**	**C**	**I**	**C**	**I**	**C**
Informed consent	**X**	**X**										
Demographic data collection	**X**	**X**										
Measures of illness control	**X**	**X**	**X**		**X**	**X**		**X**	**X**	**X**		**X**
Unplanned hospital visits	**X**	**X**	**X**		**X**	**X**		**X**	**X**	**X**		**X**
Questionnaires	**X**	**X**	**X**			**X**		**X**	**X**			**X**
Partners in Health (PIH) Scale	**X**	**X**	**X**		**X**	**X**		**X**	**X**	**X**		**X**
Feasibility and Acceptability Questionnaire (FAQ)									**X**			**X**
Flinders Program delivery	**X**		**X**		**X**	**X**	**X**	**X**	**X**	**X**		**X**
Booster session					**X**					**X**		

***I*** Intervention (Flinders Program plus usual care), ***C*** Control (waitlist plus usual care)

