#### Secondary outcome measures

The secondary outcome measures are the number of unplanned or unscheduled health care emergency department visits, quality of life, self-efficacy, time management, health-related distress, and feasibility and acceptability of a modified self-management program designed for adolescents with a chronic condition which include:

- Hospital admissions and emergency department visits due to chronic illness will be obtained from the medical records or My Health Record system if the young person is registered. An unplanned hospital admission is defined as an admission that is not part of routine illness management, not from an admission waiting list and which can be associated with a deterioration of illness control as a result of insufficient self-management practices [51]. These measures will be collected in all study participants at baseline in both standard care and intervention groups as with other measures except the feasibility and acceptability questionnaire at interval periods of 3, 6, and 12 months from baseline. The median and range of numbers of unplanned hospital admissions per person in each group will be described.

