## Data collection and management

### Plans for assessment and collection of outcomes {18a}

Patient demographic data will be collected at baseline (see Additional file 3). All data collection questionnaires are programmed in Research Electronic Data Capture (REDCap) and include Partners in Health (PIH) Scale, collected at baseline, 3, 6, and 12 months follow-up. Paediatric Quality of Life Inventory (PedsQL) version 4.0 (Teenage Report); Time Management Questionnaire; Kessler Psychological Distress Scale (K10) collected at baseline, 3 months, and 12 months follow-up. Additional data on makers of illness control and unplanned hospital admissions and emergency department visits will be obtained from the EMR at baseline, 3, 6, and 12 months follow-up. Data questionnaire on feasibility and acceptability will be collected on completion of the study at 12 months (see Additional file 4). Data will be collected and stored in REDCap a secure web-based application used for designing and managing clinical research databases. REDCap is an online data capture tool which stores data in a secure and encrypted manner on the University of Sydney server to which we have access [68]. This research data management platform is a secure web-based software platform used for the data management procedures of this trial including data collection, follow-up, and analyses. The built-in component of REDCap has been pre-prepared to accept only variables within given permissible ranges that are consistent with previous entries before going on to the next section to minimize missing values. Data collection forms pertaining to the study will also be stored in REDCap.

Prior to the commencement of the study, research staff completed the Flinders training workshop conducted over 2 days, by the lead research nurse (JG) who is an Accredited Flinders Trainer. All research staff were assessed as competent against current Flinders competency standards. The training was guided by validated manuals (Accredited Trainer: Flinders Chronic Condition Management Program Manual; The Flinders Chronic Condition Program Participant Manual) with electronic copies of all training resources and PowerPoint presentations available to ensure reproducibility and fidelity of the intervention program.

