In addition to the delivery of training required for the implementation of the intervention, a self-report evaluation checklist was developed by the research team, specifically for the study, to guide each interview and to assess fidelity ensuring that all key points are covered during each consultation. The self-report checklist is completed immediately after the consultation by the health professional delivering the intervention and is emailed to the research nurse coordinator. Follow-up quality assurance checks will also be completed by the research team as part of the study after each consultation. Information around attendance, aspects of the program covered in the first and subsequent sessions, length of consultation visits, records of all face-to-face consultations and phone contact, and the development of a care plan will be recorded. The training and self-report evaluation checklist serve to minimize technical deviations from the protocol and provide reproducible results.

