## Statistical methods

### Statistical methods for primary and secondary outcomes {20a}

Participant demographic, clinical characteristics, and study outcomes will be presented using standard descriptive statistics, including mean, standard deviation and range or median, quartiles and range for continuous variables, frequencies and percentages for categorical variables, and the Kaplan–Meier method for time to event variables. All statistical analyses will use the intention to treat principle whereby participants are analyzed in their randomized groups, regardless of treatment received. The primary outcome of the number of responses in each treatment arm will be compared using a chi-square test and the difference in proportions presented with a 95% confidence interval. Other study outcomes will be compared between randomized groups using standard tests, including chi-square tests for categorical outcomes, two-sample *t*-tests or nonparametric equivalent for continuous outcomes, Poisson regression models for count data, and log-rank test for time-to-event data. For longitudinal outcomes, statistical models that account for the correlation between repeated observations in the same participant will be used. A more detailed pre-specified statistical analysis plan is forthcoming with completion of the trial and will be made publicly available.

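### The feasibility and acceptability questionnaire is scheduled once, at programme end, with no administration when a participant stops or withdraws, so the result risks over-representing those who stay.

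*Protocol article*

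**What the plan says.** All references are to the protocol article.

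- **Status of the outcome.** Objectives and hypothesis {7} lists among the secondary objectives "feasibility and acceptability of the program to further refine its delivery under clinical conditions". Secondary outcome measures, under Outcomes {12}, names "feasibility and acceptability of a modified self-management program designed for adolescents with a chronic condition".
- **Timing.** The FAQ section states: "At the end of the self-management intervention participants will be asked to complete a semi-structured qualitative feasibility and acceptability questionnaire". Table 2 has one mark per arm on the FAQ row, at 12 months for intervention and 18 months for control. Secondary outcome measures sets the FAQ apart from the repeated collections: "as with other measures except the feasibility and acceptability questionnaire at interval periods of 3, 6, and 12 months from baseline". Section {18a} says: "Data questionnaire on feasibility and acceptability will be collected on completion of the study at 12 months".
- **Missing answers.** Follow-up data collection treats a participant as missing after three failed contact attempts at a time point. Section {20c} analyses available data by randomised group and does not impute. After withdrawal, the only outcome data described, in {14} and {20c}, are clinical outcomes taken from medical records.
- **Related records.** Section {18a} also logs, for each consultation, "Information around attendance, aspects of the program covered in the first and subsequent sessions, length of consultation visits", and {23} repeats this for audit. Sections {18b} and {20c} plan to record reasons for withdrawal; {18b} makes this conditional on the participant giving one.
- **Analysis.** Section {20a} says in general terms: "Other study outcomes will be compared between randomized groups using standard tests".

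**The concern.** A young person for whom the programme did not work is more likely to have left, or to be out of reach, by month 12 or 18 than one who liked it. With a single administration at the end and none at exit, that person's view is the one most likely to be absent. The protocol gives grounds to expect this. Trial design {8} cites the difficulty of recruiting and retaining adolescents, and Intervention description {11a} reports pilot experience that long-term attendance depends on how the programme is delivered.

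The FAQ is meant to guide refinement of delivery and the design of the adolescent version, so the views of those who leave matter for its stated purpose. Who is asked, and when, is a data-collection choice that the article states outright. A later analysis plan cannot recover answers that were never requested.

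**Working it through.** **1. The plan's own loss allowance.** Section {14} needs 54 participants (27 per group) and recruits 60. The implied loss is 1 − 54/60 = 10%. The 27 per group reproduces for 15% versus 50%, two-sided 5%, chi-square without continuity correction (power 80.2%). The present point does not depend on that calculation. The 10% is study loss to follow-up. The article gives no figure for programme discontinuation, FAQ response or approval, so the figures below are illustrations.

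**2. Bounds with nothing known about non-responders.** Let *d* be the share of starters who do not answer and *s* the approval among responders. Approval among all starters lies between

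- lower: *s*(1 − *d*), if no non-responder approves;
- upper: *s*(1 − *d*) + *d*, if every non-responder approves.

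With *s* = 0.90 (assumed):

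| *d* | Lower | Upper |
|---|---|---|
| 0.10 (implied by {14}) | 0.90 × 0.90 = 81% | 81% + 10% = 91% |
| 0.20 (assumed) | 0.90 × 0.80 = 72% | 72% + 20% = 92% |
| 0.30 (assumed) | 0.90 × 0.70 = 63% | 63% + 30% = 93% |

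At 30% loss the true figure could be up to 27 points below the reported 90% (90 − 63), or up to 3 points above it (93 − 90).

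**3. Size of the error for a given view among non-responders.** Error = *d* × (*s* − *s*₀), where *s*₀ is approval among non-responders. With *s* = 0.90 and *s*₀ = 0.50 (both assumed):

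- 10% loss: 0.10 × 0.40 = 4 points too high.
- 30% loss: 0.30 × 0.40 = 12 points too high.

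If *s*₀ = *s* the error is zero. If *s*₀ exceeds *s* the reported figure is too low.

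**4. Timing across sections.** Trial design {8} has the waitlist arm start the programme at 6 months. At month 12 they are 12 − 6 = 6 months into it, and at month 18 they are 18 − 6 = 12 months into it. Only month 18 matches an end-of-programme questionnaire for that arm, as in Table 2. Section {18a} gives 12 months without separating the arms. The two do not agree.

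**5. What an arm comparison would mean.** At the Table 2 time points both arms have had the 12-month programme. A difference in FAQ answers between arms would not compare the programme with usual care.

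**The case against.** The strongest reply is that nothing in the text limits the FAQ to completers. The FAQ section sets no attendance condition, and Table 2 schedules by arm and month. Someone who stops sessions without leaving the study stays in follow-up by telehealth, phone or email, with three contact attempts, and can still be asked. This stands. A reader might infer that dropouts are excluded by rule, but the documents do not say so. The gap concerns those who withdraw from the study or can no longer be reached, and the delay before others are asked.

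Second, reasons for leaving are not ignored: withdrawal reasons are to be recorded and used in interpretation. This also stands, but it is a partial offset. It covers withdrawal from the study rather than stopping sessions, depends on a reason being given, and does not supply the FAQ's answers on feasibility, benefit and satisfaction.

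Third, a reader might take an upward bias as established. It is not. The article gives no approval or response rate, and the bounds allow a small error in the other direction.

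Fourth, a reader might infer from {20a} that the FAQ will be tested between arms. That sentence is generic, the FAQ is described as qualitative, and detail is deferred to a later analysis plan. No such test is committed to.

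Finally, the outcome is formative and no decision threshold rests on it. That limits the weight of the point but does not remove it.

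**Conclusion.** The point holds as a risk that is cheap to reduce. The only stated measure of a named secondary outcome is collected once at programme end, with no route for those who stop or withdraw to answer at that moment, and missing answers are not imputed. The result therefore risks over-representing those who stay. Overstated acceptability is the likely direction, on the assumption that leavers are less satisfied, which is plausible but not shown in the documents. At an assumed 90% approval among responders, the figure for all starters is uncertain from 81% to 91% at 10% loss and from 63% to 93% at 30% loss. The primary outcome and its sample size are unaffected. The 12-month statement in {18a} and the 18-month mark for the waitlist arm in Table 2 conflict and need reconciling.

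**What to change.** 1. Offer the existing five-question FAQ when a participant stops the programme or withdraws, as well as at its end.
2. Report feasibility from the attendance records already kept under {18a} and {23}: the share attending the first session, each review and the booster, with everyone offered the programme, in both arms, in the denominator.
3. Report the FAQ descriptively with its response rate, and state that a difference between arms is not to be read as programme versus usual care.
4. Reconcile {18a} with Table 2 on when the waitlist arm receives the FAQ.

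The cost is one extra send of a short existing form, one table from data already logged, and a wording correction. The downside is that some leavers will not reply, so selection is reduced rather than removed; the reported response rate will show how much remains.

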### Participant timeline {13}

A schematic diagram for participant timeline is shown in Table 2.

### Sample size {14}

The primary outcome of a response to treatment is defined by improvement in disease markers listed in Table 1. We estimate that fewer than 15% of participants would show improvement in disease under usual care, and the intervention would only be considered worthwhile implementing if it can improve responses by a substantial margin. A study conducted by Rhee and colleagues, which evaluated the effectiveness of a self-management program for adolescents with asthma, found overall the intervention group reporting greater improvements in outcome measures; knowledge, self-management skills self-efficacy, and Quality of Life (QOL), than the control group [66]. A study of 54 participants (27 per group) will have 80% power at 5% two-sided alpha to detect a difference in response rates between treatment arms if the rate under usual care is 15% or less and the true difference in proportions is at least 35%, using a chi-square test. To allow for some loss to follow-up, we plan to recruit a total of 60 participants. Participants who withdraw from the study will not be replaced as the power analysis allows for attrition. Participants who withdraw from the study, may have their clinical outcomes determined from their medical records to ensure that the results of the research study can be measured accurately.

### Recruitment {15}

Potentially eligible participants will be identified by their primary treating teams, who will provide participants with information about the study, prior to their enrollment to determine the young person’s interest and willingness to participate and seek permission for a member of the research team to make contact with them. If permission is granted by the participant, a member of the research team will contact the participant either via telehealth modality, phone contact, or face to face to extend an invitation to participate in the study and provide further information as part of the formal consent process. In addition, all adolescents referred to either the Self-Management Support Service (SMS) in the Department of Adolescent Medicine or the Trapeze Service across both sites of the SCHN (Westmead and Randwick) and who meet the study criteria will be invited to participate in the study by a health professional who is not part of their clinical treatment team (Fig. 2 outlines this process).

**Fig. 2 Fig2:**
[figure not shown]
Flowchart for participant recruitment

Recruitment is planned to be undertaken over an estimated duration of 12 months and will continue until the required number of participants to meet the sample size and power requirements of the study has been reached.

Study information will be advertised on the SCHN staff intranet, and an email sent targeting potential specialist referring teams across the SCHN to assist in referral of eligible young people to the study. Research information flyers will also be used to advertise the study and displayed within various locations, including Adolescent Medicine, outpatient clinics, and adolescent ambulatory care areas at both hospital campuses. In addition, the research team has been promoting the study by collaborating with the primary treating teams to identify eligible patients to increase participant enrollment and meet the target sample size.

## Assignment of interventions: allocation

### Sequence generation {16a}

Following formal consent, the participants will be randomized. Successively, baseline data collection and measures of illness control will be collected for both the control and intervention groups. Randomization will be stratified by disease condition (diabetes, CF, renal, inflammatory bowel disease, other) and will use permuted blocks to maintain balance.

